### 2.4. Outcome Measures

The planned primary outcome is the time to diagnosis of HDP. Planned secondary outcomes include an improvement in the perceived quality of care and reduced maternal stress. Additionally, we will measure the effect of cultural tailoring and its associated impact on health equity. While this study is not powered to detect differences in the rates of severe maternal morbidity, we will evaluate this outcome as an investigational hypothesis. 

We have selected biometric, behavioral, and social identification measures that are linked to our conceptual framework and hypotheses. EHR review will provide information on the diagnosis and timing, gestational age at delivery, mode of delivery, maternal comorbidities, and participation in postpartum care. The study instruments will be applied after consent and before enrollment, during pregnancy as specified, and at six to eight postpartum.

Blood pressure. Blood pressure will be taken using the internet-enabled blood pressure equipment provided, which will be linked to the digital platform and integrated with the EHR. These devices are calibrated and tested for consistency with hospital-based medical equipment. All recorded values will be included from the first prenatal visit to 8 weeks postpartum for research objectives 1 and 2. 

Laboratory values. The results of laboratory testing used to diagnose preeclampsia will be extracted from the EHR, including the complete metabolic panel, urine protein–creatinine ratio, and other data for research objectives 1 and 2. 

Quality of Prenatal Care Questionnaire [39]. The QPCQ is a reliable and validated instrument developed to assess the perceived quality of prenatal care. Reported Cronbach’s alpha = 0.96 and inter-item correlation coefficient = 0.88. This will be completed once each trimester for research objectives 1 and 2. 

Perceived Prenatal Maternal Stress Scale (PPNMSS). This validated instrument consists of 28 items organized as four sub-scales of perceived social support, pregnancy-specific concerns, intimate partner interaction, and economic matters [40]. Cronbach’s alpha = 0.83, with an inter-item correlation coefficient of <0.9. For research objectives 1 and 2, the PPNMSS will be completed once each trimester. 

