##### Independent Variables and Covariates

The independent variable of interest for research objective 2 will be a group variable. Participants will be randomized to one of two groups: the intervention group (digital platform with RBPM and cultural tailoring) or comparison (digital platform with RBPM but no cultural tailoring). The covariates will be the age at enrollment in years, race, ethnicity, health insurance type (e.g., Medicaid, commercial, HMO), gestational age at first visit, and total number of prenatal visits. 

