##### Objective 2 and Analysis Plan

The outcome, a count variable, will be defined as the total number of recorded blood pressure readings during the prenatal period. A Poisson or Negative Binomial regression will be used to model the number of recorded blood pressure readings during the prenatal period. Interactions between the study group and race will be tested. Significant interactions between a group and race would indicate that the effect of race differed between the study groups. If an interaction is statistically significant, predicted effects with 95% confidence intervals for race by study group will be provided. Regression coefficients with *p*-values from the model will be reported.

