### 2.7. Data Approach

This study will use data both from the digital platform and the health system’s enterprise EHR. To support the cohort definitions for the randomized trial, digital platform users will be identified by a combination of referrals ordered through the Computerized Physician Order Entry (CPOE) system, matching of contributor systems (i.e., patients with RBPM integration), and industry-standard deterministic matching algorithms. Additionally, the team will use the ICD-10-CM (diagnoses), SNOMED-CT (problems), and Intelligent Medical Objects (diagnosis and problems) coding standards to identify the conditions of interest to support both the time to diagnosis outcome measurements. 

Digital platform data will consist of both manual and automatic data feeds, which will be matched using the approach outlined above. These RBPM readings will be aggregated, and user activity analysis will be aggregated and analyzed with temporal analysis using a multi-paradigm programming language. The number of blood pressure readings and user activity will be correlated with the information in the medical record to establish the relationship between engagement and outcomes. 

Many variables will be defined using EHR data recorded during perinatal care, including demographics, EPDS scores, utilization/engagement, and documentation from the delivery event. These heterogenous data elements are stored in the EHR as structured data to facilitate clean data extraction. They include diagnostics (e.g., lab orders), observations (e.g., vital signs), assessments (EPDS), and medical history (prior diagnoses and chronic conditions). 

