**Figure 2 ijerph-21-00603-f002:**
[figure not shown]
Frequency of blood pressure monitoring is specific to the diagnosis of each patient and reminders are sent to aid adherence to clinical management guidance.

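### Objective 2 counts total prenatal readings without observation time, and Section 2.7 then reads the number of readings as engagement, although pregnancy length and possibly diagnosis also change it

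*Protocol article*

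**What the plan says.** All places are in the protocol article.

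- Section 2.6.2, Objective 2 and Analysis Plan: the outcome is a count, "defined as the total number of recorded blood pressure readings during the prenatal period". On the choice of model, the same section says: "A Poisson or Negative Binomial regression will be used to model the number of recorded blood pressure readings during the prenatal period". The group-by-race interaction is tested.
- Section 2.6.2, Independent Variables and Covariates: besides age, race, ethnicity and insurance, the covariates are "gestational age at first visit, and total number of prenatal visits". Gestational age at delivery, days under observation and HDP status are not listed.
- Section 2.4, on which readings are kept: "All recorded values will be included from the first prenatal visit to 8 weeks postpartum for research objectives 1 and 2". Nothing separates readings before a diagnosis from those after it.
- Figure 2 caption: "Frequency of blood pressure monitoring is specific to the diagnosis of each patient", with reminders sent. The figure itself is not shown.
- Section 2.7: "The number of blood pressure readings and user activity will be correlated with the information in the medical record to establish the relationship". The relationship meant is that of engagement with outcomes.
- Section 2.4, on the data available: "EHR review will provide information on the diagnosis and timing, gestational age at delivery".

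**The concern.** A reading total is a fair measure of engagement only if women have similar time in which to record readings and are asked for them at similar frequency. The plan secures neither.

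A woman who delivers early has a shorter window and a lower total at the same adherence. If a new HDP diagnosis raises the number of readings requested, a diagnosed woman has a higher total at the same adherence.

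This matters most in Section 2.7. There, women with and without the outcome are compared directly, and the outcome (diagnosis or early delivery) may itself have altered the count said to measure engagement. An association could then appear, or be masked, with no difference in engagement.

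The randomised comparison is better protected, because randomisation balances entry time and baseline disease on average. It does not balance what tailoring changes afterwards. Section 2.3 expects tailoring to affect time to diagnosis among Black users and to reduce preterm birth, and both feed into the count. A higher total in the tailored arm could partly reflect earlier diagnosis or longer gestation.

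**Working it through.** **The plan's own figure.** No sample size, expected rate or dispersion is given for the count. The only calculated size is 1745, for the Cox test of time to HDP (Section 2.5). Schoenfeld's formula gives (1.960 + 0.842)² / (0.25 × ln(1.4)²) = 277.3 events, and 277.3 / 0.159 = 1744.1. The figure reproduces, and this point does not affect it.

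**Pregnancy length alone.** The weeks are assumed. Entry at week 8 gives 40 − 8 = 32 weeks with delivery at week 40, and 34 − 8 = 26 weeks with delivery at week 34. The ratio is 26/32 = 0.81. Entry at week 20 with delivery at week 40 gives 20/32 = 0.62. Gestational age at first visit can largely absorb the second contrast, but not the first.

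**Diagnosis.** All inputs except 15.9% are assumptions used only to show the range; none is a suggested schedule. Entry is at week 10 and diagnosis at week 34. Delivery is at week 39 without HDP and week 37 with it. Adherence is 60% for everyone. Requested readings per week are r0 before diagnosis and r1 after it.

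- Non-HDP count = 0.6 × 29 × r0
- HDP count = 0.6 × (24 × r0 + 3 × r1)
- HDP count with diagnosis 2 weeks earlier = 0.6 × (22 × r0 + 5 × r1)
- Arm mean = (1 − p) × non-HDP count + p × HDP count, with p = 15.9% (Section 2.5) or an assumed 25%

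| r0 to r1 | Non-HDP | HDP | HDP/non-HDP | Arm ratio, p = 15.9% | Arm ratio, p = 25% | Ratio of arm ratios |
|---|---|---|---|---|---|---|
| 2 to 2 | 34.8 | 32.4 | 0.93 | 1.00 | 1.00 | 1.00 |
| 1 to 2 | 17.4 | 18.0 | 1.03 | 1.01 | 1.02 | 1.01 |
| 2 to 7 | 34.8 | 41.4 | 1.19 | 1.03 | 1.04 | 1.01 |
| 1 to 7 | 17.4 | 27.0 | 1.55 | 1.06 | 1.09 | 1.03 |
| 2 to 14 | 34.8 | 54.0 | 1.55 | 1.06 | 1.09 | 1.03 |
| 1 to 14 | 17.4 | 39.6 | 2.28 | 1.12 | 1.17 | 1.05 |

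The last row in full, at p = 15.9%: the mean is 0.841 × 17.4 + 0.159 × 39.6 = 20.93. With earlier diagnosis the HDP count is 0.6 × (22 + 70) = 55.2 and the mean is 0.841 × 17.4 + 0.159 × 55.2 = 23.41. The arm ratio is 23.41 / 20.93 = 1.12.

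The final column is the spurious interaction when diagnosis moves by 2 weeks in both race groups and their HDP risks are 15.9% and 25%. If the shift occurred in one race group only, the spurious interaction would equal that group's arm ratio, at most 1.17 here.

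**What each correction does.** Dividing by observation time alone turns 0.93 into (32.4/27) / (34.8/29) = 1.00, so it removes the length effect. It turns 2.28 into (39.6/27) / (17.4/29) = 2.44, so it does not remove a diagnosis-driven change in frequency. The pre-diagnosis rate is 0.6 × r0 per week in both groups, and the share of requested readings is 0.60 in both. Either gives a ratio of 1.00 in every row.

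**The case against.** The strongest reply has four parts.

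First, the mechanism through diagnosis rests on a figure that is not shown. Section 2.2 describes Figure 2 in terms of risk status, so the caption may refer to a baseline category and not to a schedule that changes during follow-up. This stands, and the diagnosis part must stay conditional. The length part does not depend on it.

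Second, the covariates already adjust for exposure. They do so in part: gestational age at first visit handles the start of observation, and the number of visits is a rough proxy for its length. But the visit count is post-randomisation and may rise with HDP, and neither variable captures the delivery or diagnosis date.

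Third, an offset is ordinary analysis-plan detail that a condensed article may omit. That is fair for the offset alone. The article does, however, fix the outcome as a total and use the number of readings as engagement in Section 2.7.

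Fourth, the total of all readings in all randomised women is a defensible intention-to-treat quantity. This also stands, and is a reason not to replace it with a count cut at diagnosis. Such a window would end at an event that tailoring may change. It would also be undefined for women already hypertensive at entry, whom Section 2.5 does not exclude.

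A reader might go further and infer that the Section 2.7 correlation is reverse-causal. The documents support only that it may be: the schedule is not visible, the text speaks of a relationship and not of cause, and user activity and temporal analysis are planned alongside. A reader might also infer that the interaction test will have an inflated error rate because Poisson is named. The article equally names negative binomial, gives no dispersion, and may leave the choice to an analysis plan.

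**Conclusion.** The point holds in a limited form. As written, the objective 2 total mixes engagement with pregnancy length and, if the requested frequency changes on an HDP diagnosis, with diagnosis too.

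The engagement-outcome analysis in Section 2.7 is the most exposed, with a ratio of about 0.93 to 2.28 at equal adherence. The randomised contrasts move less: 1.00 to 1.17 between arms for a 2-week shift in diagnosis, and 1.00 to 1.05 for group by race when the shift is the same in both race groups. All these sizes rest on assumed frequencies, dates and adherence; the documents give no figure that would narrow them.

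**What to change.** 1. **Main objective 2 model.** Keep all randomised women and all prenatal readings, and add log(days from randomisation to delivery) as an offset.
2. **Supporting analysis.** Report the reading rate before HDP diagnosis, or readings as a share of those requested. State a rule for women already hypertensive at entry, for example using the share of requested readings for them.
3. **Section 2.7.** When relating engagement to HDP, use the reading rate before diagnosis per day at risk. When relating it to delivery outcomes, use a rate and not the prenatal total.

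The cost is wording and a little more analysis. Diagnosis timing and gestational age at delivery are already to be extracted, and platform readings are already to be analysed over time. The share-of-requested measure also needs each woman's requested frequency over time, which should be confirmed as recorded. The pre-diagnosis analysis stays supportive only, because its window ends at a post-randomisation event. Phase 2 follows phase 1, so this can be settled before phase 2 starts.

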### 2.3. Planned Analysis: Time to Diagnosis of Hypertensive Disorders of Pregnancy

A planned analysis will be conducted, with the aim of completing the research objectives, sequentially in two phases. The first research objective will be completed as phase 1 using a time-to-event strategy and intent to treat. In this phase, we will evaluate the days to diagnosis of HDP when using the digital platform, with an active comparison group. The comparison group will receive a digital platform that offers educational content but not RBPM. Patients will be assigned 1:1 using a random number generator to either the intervention (digital platform plus RBPM) or active comparison (digital platform). The hypotheses are the following:Diagnosis of previously unrecognized chronic hypertension will increase with use of RBPM.RPBM and use of the digital platform will decrease the days to diagnosis of HDP.RBPM will decrease the time to diagnosis for all users regardless of demographic characteristics.

When phase 1 is completed, our team will incorporate culturally responsive social identification strategies to increase the engagement among Black patients. The content for cultural tailoring will be developed during phase 1 under a separate protocol not described here. The second research objective will be achieved by evaluating this tailoring in a randomized controlled trial as a second phase. The hypotheses are the following: Cultural tailoring will promote social identification and mediate treatment effects on the time to diagnosis of HDP among Black users, narrowing the equity gap in outcomes.Cultural tailoring will improve the perceived quality of care, reduce stress, and improve social support. These benefits will result in additional improvements in perinatal outcomes, such as fewer preterm birth and depression symptoms.

We further anticipate that social identification will create a consistent “brand” for the program (common desirable features, consistent imagery, look and feel) and will affect the time to diagnosis of HDP outcomes [38]. Recognition of the intervention and its tailored features will promote engagement and participation.

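### Objective 2 tests the group-by-race effect on readings only as a ratio and withholds race-by-arm predictions unless that test is significant, so a change in the absolute gap could go unreported

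*Protocol article*

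**What the plan says.** Section 2.6 of the protocol article says that the objective 2 analysis centres on health equity. The only analysis then specified is under the heading Objective 2 and Analysis Plan in section 2.6.2.

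- Outcome: "The outcome, a count variable, will be defined as the total number of recorded blood pressure readings during the prenatal period".
- Model: "A Poisson or Negative Binomial regression will be used to model the number of recorded blood pressure readings during the prenatal period". The link function is not named.
- Test: "Interactions between the study group and race will be tested".
- Interpretation: "Significant interactions between a group and race would indicate that the effect of race differed between the study groups". No scale is named.
- Condition on reporting: "If an interaction is statistically significant, predicted effects with 95% confidence intervals for race by study group will be provided".
- Reported in any case: "Regression coefficients with *p*-values from the model will be reported".

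The arms are the platform with remote monitoring, with or without tailoring. The covariate list includes race, so participants who are not Black are randomized to tailored content as well. The article gives no expected counts by race and no sample size calculation for objective 2.

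**The concern.** Whether a race difference changes between arms depends on whether it is measured as a ratio or as a difference. With a log link the product term answers only the ratio question. When the two races start from different means, the ratio can stay fixed while the difference moves.

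The reporting condition makes this matter. If the ratio-scale term is not significant, the reader is promised coefficients and p-values but no predictions by race and arm. With the model output alone, a reader could rebuild point predictions at a chosen covariate profile, but could not attach an interval to a change in the gap. At stake is whether an equity-focused analysis could be summarized as showing no differential effect while the number of readings separating Black and white participants had grown.

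**Working it through.** **Inputs.** The model, the test and the reporting condition come from section 2.6.2. The log link is assumed, as the standard link for both named models. All means, multipliers and dispersions below are assumptions, because the article gives none.

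**The plan's own figure.** There is none for objective 2. The only sample size, 1745 in section 2.5, is for the objective 1 Cox model, and it reproduces. Events = (1.960 + 0.842)² / (0.25 × (ln 1.4)²) = 277.3, and 277.3 / 0.159 = 1744.1, rounded up to 1745. It is not affected by this point and is used below only as a plausible phase 2 size.

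**Algebra.** Let the untailored means be W (white) and B (Black), and let tailoring multiply them by m and b.

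- Exponentiated interaction = (Bb/B) / (Wm/W) = b/m.
- Change in the gap (white minus Black) = W(m − 1) − B(b − 1).
- If b = m, the interaction is exactly 1 and the gap changes by (W − B)(m − 1). That is zero only if W = B or m = 1.

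**Proportionally equal effects (b = m).**

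| Untailored (white v Black) | Multiplier in both | Tailored | Interaction | Gap |
|---|---|---|---|---|
| 60 v 40 | 1.1 | 66 v 44 | 1.00 | 20 to 22 |
| 60 v 40 | 1.2 | 72 v 48 | 1.00 | 20 to 24 |
| 60 v 40 | 1.3 | 78 v 52 | 1.00 | 20 to 26 |
| 60 v 54 | 1.3 | 78 v 70.2 | 1.00 | 6 to 7.8 |

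In the second row, (48/40)/(72/60) = 1.20/1.20 = 1.00 and 20 × 0.2 = 4, which is the growth in the gap.

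**When the two scales agree.** If only Black participants respond (60 v 40 becomes 60 v 46), the interaction is 1.15 and the gap falls from 20 to 14. Both scales then show the difference shrinking.

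**How often the widening would go unreported.** Simulation: negative binomial counts, N = 1745, 1:1 allocation, 35% Black and the rest taken as white, 60 v 40 with both multiplied by 1.3, 1000 runs.

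| Dispersion | Log-scale interaction significant | Difference-scale test detects wider gap |
|---|---|---|
| 0.3 | 4.5% | 48% |
| 0.5 | 6.0% | 32% |
| 1.0 | 4.1% | 19% |

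The log-scale test rejects at about its nominal rate, as it should, since its null hypothesis is true. In 94.0% to 95.9% of runs no race-by-arm prediction would be promised, although the true gap grew from 20 to 26.

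**The case against.** The strongest reply is that nothing in section 2.6.2 is false. A significant product term does show that the race effect differs on the model's scale, and a ratio is the conventional scale for counts. Dependence on the link is a property of every generalized linear model. The article never defines a gap as a difference. This stands, so the point concerns what is reported and does not make the model wrong.

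The conditions are also assumptions. No count by race is given. Section 1 describes unequal digital access, which suggests fewer readings among Black participants. It also says that Black women more often enter pregnancy with chronic hypertension, and the Figure 2 caption ties monitoring frequency to diagnosis, so they might record more. If only Black participants respond to content aimed at them, the scales agree. This too stands, and it leaves the likelihood of the problem unknown.

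A reader might infer that the plan would declare a narrowed gap when the gap had in fact widened. The documents do not support that:

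- Section 2.6.2 never equates a positive term with narrowing.
- The phrase "narrowing the equity gap in outcomes" in section 2.3 belongs to a hypothesis about time to diagnosis, not about readings.
- A case such as 60 v 40 becoming 66 v 45 (gap 20 to 21) has an interaction of (45/40)/(66/60) = 1.023. With a standard error of 0.057 to 0.101 (N = 1745, dispersion 0.3 to 1.0), z is 0.2 to 0.4 and power is about 6% to 7%.
- Larger assumed effects can reach significance. With 60 v 30 becoming 78 v 45 (gap 30 to 33), the term is significant in 29% to 68% of runs. Predictions are then promised and, if given as counts, would reveal the wider gap.

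Finally, the prediction scale and contrasts are often left to an analysis plan. That is fair for details the article omits, but the condition on significance is a rule it states.

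**Conclusion.** The point holds as an improvement to a stated reporting rule. In the only analysis specified for objective 2, a non-significant ratio-scale interaction removes the promised race-by-arm predictions. In that case a proportionally equal effect can widen the absolute difference in readings without its being tested or shown: from 20 to 24 in the 60 v 40 illustration with a 20% rise in both.

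This rests on three assumptions: a log link, different starting means by race, and a rise in readings among white as well as Black participants. The article does not state the link and gives no counts, so neither the size nor the probability can be fixed from it.

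The ratio of rate ratios is a valid measure and should stay. The difference scale belongs beside it, and neither scale should be able to veto a conclusion on the other, since the article gives no basis for such a rule.

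**What to change.** In section 2.6.2, under Objective 2 and Analysis Plan:

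1. Remove the condition that the interaction be significant before race-by-arm predictions are given.
2. From the same fitted model, report mean readings by race and arm. Report also the difference-in-differences in mean readings (Black minus white, tailored minus untailored) with a robust or bootstrap 95% CI.
3. Report these beside the ratio of rate ratios with its own CI, whatever the interaction p-value.
4. Name the scale whenever a change in the race effect is claimed.

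The cost is a few lines of wording and a post-estimation step. No extra data or participants are needed. The downside is two scales to report, which may point different ways and will then need explaining. The simulation also suggests that the difference-scale estimate may be imprecise at this size, so its interval matters more than its p-value.

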### 2.5. Sample Size and Recruitment

The sample size was calculated using PROC POWER in SAS for a two-sided Score test in the Cox proportional hazard regression of the time to diagnosis of an HDP in the study group, with a binary variable taking on the values of intervention (digital platform plus RBPM) or active comparison (digital platform). The proportion of total participants in the intervention group was set at 50%. A hazard ratio of 1.4 for the study group was used as the effect size. The overall probability that a participant would be diagnosed with an HPD was set at 15.9% [43]. The total number of subjects needed to achieve a power of 80% with a significance level of 0.05 was determined to be 1745. 

Overall, HDP affects 15.9% of delivery hospitalizations in the US [43], and the prevalence is higher among patients served by the study site. In 24 months, our system provides prenatal care to over 3000 patients. Given this patient volume and prevalence, we considered the estimated sample size feasible with a 60% enrollment rate, which is consistent with the engagement with prior research studies in our setting of similar durations. We anticipate that the required cohort for each research objective will be enrolled within the desired timeline. The total active participant enrollment time for the planned protocol will be a total of 48 months: 24 months for phase 1, and 24 months for phase 2. 

All people presenting at the study site for prenatal care will be invited to participate at their initial prenatal visit by a study research coordinator. Individuals younger than 18 years will be excluded. Over 35% of patients receiving prenatal care at our facility identify as Black, which will allow us to test for the desired sub-group effects related to social identification. Randomization will occur at the time of enrollment, and baseline measures will be completed. Participants will receive USD 25 at the time of enrollment and each time they complete study data collection (enrollment, and then each subsequent trimester and postpartum) in recognition of the additional time required to complete these study materials. Survey data will be compiled using REDcap 14.2.1, a software distributed by Vanderbilt University in Nashville, Tennessee, United States, for non-commercial secure survey data collection, at enrollment and the subsequent timepoints.

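### Objective 2 gives race-specific tailoring effects with confidence intervals only after a significant interaction, and no calculation supports the sub-group statement in section 2.5

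*Protocol article*

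**What the plan says.** The abstract of the protocol article defines objective 2 as testing cultural tailoring for Black participants. Section 2.3 adds the phase 2 hypothesis that tailoring acts on time to diagnosis of a hypertensive disorder of pregnancy (HDP) among Black users and narrows the equity gap.

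The section Objective 2 and Analysis Plan (under 2.6.2) models the number of prenatal blood pressure readings by Poisson or negative binomial regression and tests group-by-race interactions. The reporting rule is: "If an interaction is statistically significant, predicted effects with 95% confidence intervals for race by study group will be provided". The only output promised without a condition is the model's coefficients with p-values. Objectives 1.A and 1.B, by contrast, report hazard ratios and odds ratios with confidence intervals unconditionally.

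On size, section 2.5 states: "The sample size was calculated using PROC POWER in SAS for a two-sided Score test in the Cox proportional hazard regression", for the contrast of the platform with and without remote blood pressure monitoring (RBPM). The same section then says: "Over 35% of patients receiving prenatal care at our facility identify as Black, which will allow us to test for the desired sub-group effects", qualified as those connected with social identification. It also says: "We anticipate that the required cohort for each research objective will be enrolled within the desired timeline". It derives only one cohort size.

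**The concern.** The effect of tailoring in Black participants is the target of objective 2, so whether it is shown with its uncertainty should not depend on a significance test. Under the stated rule, a non-significant interaction leaves the reader without a race-specific effect and interval, which is when the interval is most needed to tell a small effect from an imprecise one. Where the interaction is significant, the displayed effects have passed a filter that favours large estimates and will tend to overstate the difference.

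The sub-group sentence in section 2.5 adds to this. It presents the share of Black patients as sufficient for the tests, but a share is not a power statement. A reader or funder could take 80% power to extend to the equity question, for which nothing was calculated.

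**Working it through.** **1. Reproduce the plan's figure.** Inputs from section 2.5: two-sided 0.05, power 80%, 1:1 allocation, hazard ratio (HR) 1.4, event probability 15.9%.

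Events = (1.960 + 0.842)² / (0.25 × ln(1.4)²) = 7.849 / (0.25 × 0.1132) = 277.3. N = 277.3 / 0.159 = 1744.1, so 1745. The stated figure is correct for the overall phase 1 contrast.

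**2. Apply the same formula to Black participants.** Three inputs are assumptions:
- Phase 2 also enrols 1745; no phase 2 size is given.
- HR 1.4 is carried over. It was set for RBPM against no RBPM, whereas both phase 2 arms have RBPM.
- The Black share is 35% and incidence 15.9%. Section 2.5 says the share is over 35% and that site prevalence is higher than 15.9%, so this is the low end.

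Events = 1745 × 0.35 × 0.159 = 97.1, in about 611 participants.

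Power = Φ(ln(1.4) × √97.1 / 2 − 1.96) = Φ(1.658 − 1.960) = Φ(−0.302) = 38%.

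Detectable HR at 80% power = exp(2.80 / (√97.1 / 2)) = exp(0.569) = 1.77.

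**3. Range over more favourable inputs, at HR 1.4.**

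| N | Black share | HDP incidence | Events in Black participants | Power |
|---|---|---|---|---|
| 1745 | 35% | 15.9% | 97 | 38% |
| 1745 | 35% | 20% | 122 | 46% |
| 1745 | 35% | 25% | 153 | 55% |
| 1745 | 35% | 30% | 183 | 62% |
| 1800 | 40% | 30% | 216 | 70% |

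The 1800 is 3000 patients × 60% enrolment, from section 2.5. At N = 1745 and 35% Black, 80% power would need an incidence of about 278 / 611, roughly 46%.

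**4. The count of readings.** This is the outcome the objective 2 section actually models. The documents give neither a mean nor a dispersion, so every input here is assumed. Take 611 Black and 1134 other participants, a mean of 60 and a dispersion k of 0.3 to 1.0. The standard error of the log interaction ratio is √[(k + 1/60) × 4 × (1/611 + 1/1134)], which is 0.056 to 0.101. Power is then 70% to 28% for an interaction ratio of 1.15, and over 99% to 74% for a ratio of 1.30. The answer depends entirely on values the documents do not supply.

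**5. What the unconditional output gives.** With a group term, a race term and their interaction in the model, the coefficients yield a point estimate for Black participants, either directly or as a sum of two terms, depending on the reference category. No interval is promised. Where the effect is a sum, its standard error is not among the reported items.

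**The case against.** The strongest case on the other side has four parts.

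First, coefficients with p-values are reported in any case. That stands. A reader might infer that a non-significant interaction would leave no estimate at all for Black participants. The document does not support this; what is withheld is the race-specific effects with intervals.

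Second, the 38% describes a time-to-event comparison that section 2.6.2 does not plan, since the analysis there is of reading counts. That stands too. The figure bears on the time-to-diagnosis hypothesis in section 2.3, not on the planned count model, and it borrows an effect size and a sample size from phase 1. It is also a low-end value. None of this supplies the missing calculation, and no input set in the table reaches 80%.

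Third, the 35% share may be adequate for the count outcome. It may be. A reader might infer that the count interaction is underpowered and a non-significant result likely. With no mean or dispersion in the documents, neither can be said.

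Fourth, an article may leave detail to the full plan. This disposes of two further inferences. One is that race will be coded in many categories and so dilute the test; no coding is given. The other is that the phase 1 hypothesis, "RBPM will decrease the time to diagnosis for all users regardless of demographic characteristics", lacks a matching analysis, which may be in a document not shown. The conditional rule and the sub-group sentence are different: both are written into the article.

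**Conclusion.** The point holds in two parts.

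The main part needs no arithmetic. The article fixes a rule that ties race-specific effects and their 95% CIs to a significant interaction, on the question objective 2 exists to answer. The harm is loss of precision in the report and selection of what is displayed, not total absence of an estimate.

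The secondary part is that the sub-group sentence has no supporting calculation, because 1745 was derived only for the phase 1 overall contrast. For time to diagnosis in Black participants, power at HR 1.4 is about 38% on the document's own 35% and 15.9%, 55% at 25% incidence, and about 70% with N = 1800, 40% Black and 30% incidence. All three assume a phase 2 cohort of 1745 to 1800 and an HR never set for tailoring. No claim of low power is made for the reading count.

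**What to change.** In Objective 2 and Analysis Plan, delete the significance condition. State that the tailoring effect in Black participants, the effect in other participants, and the Black versus other interaction will each be reported with a 95% CI, whatever the interaction p-value.

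In section 2.5, state that 1745 applies to the objective 1 main effect. Replace the unqualified sub-group sentence with the detectable effects and their assumptions. For time to diagnosis in Black participants this is an HR of about 1.77, given 1745 enrolled, 35% Black and 15.9% incidence, with the range for higher incidence. For the reading count, the sponsor should supply a mean and dispersion before any detectable effect is stated.

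The cost is wording in the analysis and sample-size sections, with no additional participants. The downside is that the stated sub-group capability becomes less favourable.
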